## Early Withdrawal

**Personal reasons**

As stated in the Informed Consent Form, a subject may withdraw from the study for any reason at any time.

**Removal by Qualified Investigator:**

Subject may be discontinued at the discretion of the Qualified Investigator. A subject leaving the study prematurely will not be replaced by another. Criteria for removal of subjects from the study will include:

**Clinical reasons**

A subject may be withdrawn from the study if, in the opinion of the Qualified Investigator, it is not in the subject's best interest to continue. This includes but is not limited to adverse events related to the test supplement causing clinically significant illness, the need for prohibited concomitant medication or any participant who meets exclusion criteria during the trial. All serious adverse events will result in withdrawal from the trial. Participants who experience exacerbation of any current condition and require additional intervention or a change in their current intervention will be withdrawn from the trial.

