## Inclusion Criteria

1. Male or female adults with mild knee joint pain.
2. Subjects who have given voluntary, written, informed consent to participate in the study.

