## Concomitant Medications

Subjects who are currently taking any prescribed medications must agree to maintain their current method and dosing regimen during the course of the study.

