## Visit 1 – Screening and enrollment

At screening, a Subject Information and Consent Form will be given to the potential subject. The subject will read the information carefully and will be given the opportunity to seek more information if needed. The subject will also be provided with the option of taking the consent form home to review prior to making his or her decision. If agreeable, the subject will sign the consent form and receive a duplicate. Once consent has been obtained, the following assessment will proceed.

- Review of the inclusion/exclusion criteria
- Review of medical history and concomitant therapies
- Collection of demographic information such as gender, age, alcohol consumption and smoking habits

Eligible subjects will be randomized and take baseline assessment.

Baseline assessments will include:

- Height, weight and BMI
- Japanese Knee Osteoarthritis Measure (JCOM)
- The Japanese Orthopedic Association knee rating score (JOA score)
- Blood and Urine analysis
- Range of motion (ROM) of the knee

Subjects will receive test supplements and administration diary.

Subjects will be instructed in detail by site personnel about the dosing regimen. The first dose of study product is to be taken the day at the dinner on the day taking the baseline assessment (Day 1).

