## Visit 3 – Week 8 End of Study (Day 31: 29 - 37)

Subjects will return to the clinic on day 31; Day 29– 37 will be possible according to the convenience of the subject.

Remaining test supplement in the original packaging will be returned.

Visit 3 assessments will include:

- concomitant therapies
- any adverse events
- Japanese Knee Osteoarthritis Measure (JCOM)
- The Japanese Orthopedic Association knee rating score (JOA score)
- Blood and Urine analysis
- Range of motion (ROM) of the knee
- Study diaries will be collected and reviewed.

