### JKOM and JOA

Subjects will fill JKOM questionnaire by his/her own.

Orthopedist will fill JOA score list interviewing subject.

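### The exacerbation rule removes subjects whose knee pain flares before Visit 3 from the trial with no planned JKOM or JOA, so loss of the primary score depends on the outcome (minor)

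*Protocol*

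**What the plan says.** The Protocol's text on Early Withdrawal, under Clinical reasons, first gives the Qualified Investigator discretion to withdraw a subject. It then sets two mandatory rules. One is for serious adverse events: "All serious adverse events will result in withdrawal from the trial". The other is the rule at issue: "Participants who experience exacerbation of any current condition and require additional intervention or a change in their current intervention will be withdrawn from the trial".

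Other parts of the Protocol bear on that second rule:

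- **Inclusion Criteria:** "Male or female adults with mild knee joint pain". The knee condition is therefore a current condition of every subject.
- **Exclusion Criteria and Concomitant Medications:** only biological treatment for knee pain is barred. Subjects on other prescribed medication "must agree to maintain their current method and dosing regimen during the course of the study".
- **Visits 1 to 3 and Appendix 1:** JKOM (also printed JCOM) and JOA, the two primary outcomes, are taken at Visit 1 and Visit 3. Visit 2 has neither score and may be a phone call. No exit visit is described. For Visit 3, "Subjects will return to the clinic on day 31", with a window of Day 29 to 37.
- **Removal by Qualified Investigator:** "A subject leaving the study prematurely will not be replaced by another".
- **8.2 Analytical Populations and Analysis Plan:** the effectiveness analysis uses the per-protocol set. That set requires at least 80% compliance, no major violation and completion of all visits. Subjects below 80% are dropped from further analysis.
- **Safety sections:** worsening of a pre-existing condition is reported as an adverse event and followed until it resolves or stabilises. No outcome score is attached to that follow-up.

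**The concern.** The rule takes the subject out of the trial, not just off the supplement, and what triggers it can be the outcome the trial measures. A subject whose knee gets bad enough before Visit 3 to need a new or changed treatment leaves with only a baseline JKOM and JOA. Whether the primary score exists then depends on how the knee is doing.

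If krill oil reduces knee symptoms, more placebo than krill subjects would meet the rule. The placebo completers would look better than the placebo arm as randomised, and the observed difference would shrink. An SAP could add an analysis set or an imputation, but it could not restore a score that the visit schedule never collects. That is why this belongs to the Protocol.

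**Working it through.** **Step 1: the reading.**

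| Link | Where in the Protocol | Status |
|---|---|---|
| Withdrawal is mandatory and from the trial | Clinical reasons | Stated |
| The knee counts as a current condition | Inclusion Criteria; no exemption anywhere | Plain reading, not stated |
| A change of ordinary knee medication can trigger it | Exclusion Criteria, Concomitant Medications | Follows from the two |
| No JKOM or JOA at exit or afterwards | Visits 1 to 3, Appendix 1 | Not scheduled; not expressly forbidden |
| Such a subject is outside the efficacy set | 8.2 Analytical Populations | Stated (all visits must be completed) |
| Worsening first raised at Visit 3 is scored | Visit 3 procedures | Stated; limits the problem to earlier flares |

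**Step 2: size.** The Protocol gives no withdrawal rate, outcome SD or expected effect, so there is no planned figure to reproduce. What follows is an illustration.

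From the Protocol: 25 subjects per arm.

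Assumed:
- Untreated Day 31 change Y (higher = worse) has SD 1, and the true benefit is d = 0.5 SD.
- A latent need for treatment L has SD 1 and correlation r with Y. It is lower by s in the krill arm.
- A subject is withdrawn when L exceeds c = z(1 - p), where p is the placebo withdrawal proportion: 4%, 8%, 12% or 20% (1, 2, 3 or 5 of 25).

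Write λ(x) = φ(x)/Φ(x). Among completers:

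- placebo mean = -r·λ(c)
- krill mean = -d - r·λ(c + s)
- understatement = r·[λ(c) - λ(c + s)]

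Worked case, p = 8%: c = 1.405, λ(c) = 0.1616, λ(c + 0.5) = 0.0669. With r = 0.5 and s = 0.5 the understatement is 0.5 × (0.1616 - 0.0669) = 0.047 SD, so 0.453 is observed in place of 0.5. Krill withdrawal is 2.8%.

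| Understatement (SD) | p = 4% | 8% | 12% | 20% |
|---|---|---|---|---|
| (a) r = 1, s = 0.5 (sharp cut-off, near upper bound) | 0.058 | 0.095 | 0.124 | 0.172 |
| (b) r = 0.5, s = 0.5 | 0.029 | 0.047 | 0.062 | 0.086 |
| (c) r = 0.5, s = 0.25 | 0.017 | 0.027 | 0.035 | 0.048 |

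The standard error of the difference is √(2/25) = 0.283 SD. At 4-8% in (b) and (c), the understatement of 0.017-0.047 SD is 0.06-0.17 standard errors. With d = 0 and s = 0 the two λ terms cancel and the bias is zero.

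**Step 3: would keeping Visit 3 be enough?** Suppose every withdrawn subject returns and rescue has improved the score by g SD. The remaining understatement is g × (placebo minus krill withdrawal proportion). At p = 8% in (b) the difference is 0.080 - 0.0284 = 0.0516:

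- g = 0.5: 0.026 SD
- g = 1: 0.052 SD
- present rule: 0.047 SD

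Break-even is g = 0.0474/0.0516 = 0.92 in (b), 0.89 in (c) and 1.83 in (a). A post-rescue Visit 3 score alone may therefore help little, or do worse. This is the reason for also taking a score before rescue.

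**The case against.** **The rule has a purpose.** Prescribed treatment is meant to stay constant. Removing subjects whose treatment changes keeps rescue effects out of the comparison and fits a per-protocol pilot. This stands as a reason to flag or separate post-rescue scores. It is not a reason to collect none. Stopping the supplement and treating the flare protects the subject equally well.

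**Few subjects may be affected.** Three things must coincide: a worsening, a need for changed treatment, and action before Visit 3, within about 30 days of mild pain. This stands. The larger figures in the table need a sharp cut-off or 3 to 5 of 25 placebo subjects changing treatment, and nothing in the Protocol points to such rates. In (b) at 4% and 8%, two-sided 5% power for a true 0.5 SD falls from about 41% to about 37% and 35%.

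**The wording may mean other illnesses.** The Protocol does not say so. If that was the intent, exempting the knee is a one-line repair, but knee rescue would then need handling of its own.

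**Analysis sets belong in the SAP.** Partly right. The SAP is not at hand, and the absence of a further efficacy set is not the point here. The withdrawal rule and the assessment schedule are Protocol matters.

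**Stronger readings that are not supported.** A reader might infer that every subject whose knee worsens loses the primary score; Visit 3 still scores worsening first raised there. A reader might infer that the rule could produce a spurious benefit; with no true effect and equal withdrawal, the model gives no bias. A reader might extend the argument to the serious adverse event rule; the Protocol expects no such events, and the figures here do not concern them.

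**Conclusion.** The point holds, at minor severity, for flares acted on before Visit 3. The rule and the schedule together make loss of the primary score depend on the outcome.

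The likely direction, if krill oil works, is an understated benefit. That rests on more placebo than krill subjects meeting the rule; if the arms lost subjects in another pattern, the direction could differ. The size cannot be calculated from the Protocol. For 1 or 2 of 25 placebo subjects and a correlation of 0.5, it is a small fraction of the standard error. The withdrawal rates, the 0.5 SD effect, the correlation and the arm shift are all assumptions.

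The case for acting is that the change is cheap and the missing score cannot be recovered later.

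**What to change.** **Clinical reasons.** Under the exacerbation rule, replace withdrawal from the trial with stopping the test supplement. Unless consent is withdrawn, keep the scheduled Visit 3 (Day 29 to 37). Where feasible, and without delaying care, record JKOM and JOA before the treatment change. Record the stop date, the reason and any new knee treatment.

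**Appendix 1.** Add the pre-change JKOM and JOA.

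**8.2 Analytical Populations and Analysis Plan.** Limit the deletion of subjects below 80% compliance to the per-protocol analysis. Add an analysis, using the generalized linear model already planned for the primary outcomes, in all randomised subjects with any post-baseline JKOM or JOA, whether from Visit 3 or exit. Show it three ways:

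1. with post-rescue Visit 3 scores;
2. without them;
3. with the pre-rescue exit score in their place, used also when Visit 3 is missing.

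Defining the set by any post-baseline score matters: a set limited to subjects with a Visit 3 value would leave out those who give only an exit score.

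**Reporting.** Give the number stopped under the rule, by arm.

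**Cost.** Wording changes that may need ethics review, one extra JKOM and JOA for the few subjects affected, and one added analysis with the planned model. Neither extra score is clean. Post-rescue scores mix in the effect of rescue, and exit scores taken at a flare may overstate the benefit, so both are shown. JOA will stay missing for subjects who cannot attend, because "Orthopedist will fill JOA score list interviewing subject".

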**Protocol violation**

Any subject found to have entered this study in violation of the protocol will be discontinued from the study at the discretion of the Qualified Investigator. This will include any subject found to have been inappropriately enrolled (did not meet eligibility criteria). Subject non-compliance includes not showing up for study visits, not taking the test supplement as directed, or refusing to undergo study visit procedures.

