# STUDY DESIGN

This is a single-center, randomized, double-blind, placebo-controlled, 2-arm parallel group study. This study will consist of a 30 days administration period.

The planned sample size for this study is 50 healthy older adults, with 25 subjects randomized equally to each of the two-study arms in a double-blind manner.

| **Study Arm** | **Subject Number** |
| --- | --- |
| Krill Oil | N = 25 |
| Placebo | N = 25 |
| **Total** | **N = 50** |

In order to evaluate the goals of the study, assessments will be conducted at Visit 1 (Day 1) before administration of the test supplement (baseline), and Visit 3 (Day 31). Subject will visit or will be contacted by phone after 2 weeks of ingestion (Visit 2) in order to monitor adverse events and changes in concomitant medications as well as to foster compliance with the study dosing regimen.

The study will be conducted at a single site at Fukushima Orthopedic Clinic, Tochigi, Japan.

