## Visit 2 – Week 2 (Day 14 ± 3)

Subjects will return to the clinic and the following will be discussed to reinforce product compliance:

- review of current conditions, concomitant therapies and adverse events
- compliance with test supplement

The Visit 2 can be performed via phone call.

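### Imperfect dosing is an open-ended, discretionary ground for removal from the study, so a subject who could still meet the 80% rule may lose the only post-baseline assessments

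*Protocol*

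**What the plan says.** The Early Withdrawal part of the protocol gives the investigator a general power under Removal by Qualified Investigator: "Subject may be discontinued at the discretion of the Qualified Investigator". It then introduces a list: "A subject leaving the study prematurely will not be replaced by another. Criteria for removal of subjects from the study will include". Two headings follow, Clinical reasons and Protocol violation. The second ends with this sentence: "Subject non-compliance includes not showing up for study visits, not taking the test supplement as directed, or refusing to undergo study visit procedures". It gives no number of missed doses and does not separate stopping the supplement from leaving the study.

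Elsewhere the protocol sets these rules:

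- **Outcome timing.** JKOM, JOA, blood and urine are taken at Visit 1 and Visit 3 (Study Design, Laboratory Analysis, Appendix 1). No assessment at or after removal is described.
- **Visit 2.** This contact may be by phone. It reviews current condition, concomitant therapies, adverse events and compliance, and at it "the following will be discussed to reinforce product compliance". Study Design gives its purpose as monitoring adverse events and medication changes "as well as to foster compliance with the study dosing regimen".
- **Dosing rule for analysis.** Section 8.2 admits to the per-protocol population subjects with at least 80% of doses, no major violation and every visit attended. The Compliance section bases the percentage on capsules returned at Visit 3.
- **Effectiveness analysis.** The Analysis Plan describes it on the per-protocol population only.

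**The concern.** The protocol has two dosing standards that act at different times. The 80% rule applies at the end, on a capsule count, and tolerates a fair number of missed doses. The removal criterion can be used at any time, on any departure from directed dosing, before that count exists. An investigator who uses it after Visit 2 may take out of the study someone whom the 80% rule would have kept.

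Such a subject is not replaced and misses Visit 3, so fails the attendance condition of Section 8.2 whatever the capsule count would have been. The Visit 3 JKOM, JOA and laboratory results would not exist, and no later analysis rule could recover them. That makes this a matter of trial conduct for the protocol, not one that a statistical analysis plan could settle.

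**Working it through.** **Inputs.** 8 capsules a day, 4 at breakfast and 4 at dinner (Directions). First dose at dinner on Day 1 (Visit 1). 30 days of administration and 25 subjects per arm (Study Design). 80% threshold (Section 8.2). Visit 2 on Day 14 ± 3 by its heading, Day 15 in Appendix 1. Visit 3 on Day 31, window Day 29 to 37.

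**What the 80% rule allows.**
- Capsules due: 4 (Day 1 dinner) + 29 × 8 (Days 2 to 30) + 4 (Day 31 breakfast) = 240.
- Needed: 0.80 × 240 = 192.
- May be missed: 240 − 192 = 48, or 48/8 = 6 full days.
- With Visit 3 on Day 29, the expected count is 224 or 232, depending on whether Day 1 and the visit day count in half or whether 29 full days are counted. The rule then needs 180 or 186 and allows 44 or 46 to be missed.

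**What Visit 2 can reveal.** Assume the breakfast dose has fallen due on the day of Visit 2 and the dinner dose has not. On Day d, capsules due = 8(d − 1). The lowest number taken that can still reach 192, with full dosing afterwards, is 8(d − 1) − 48.

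| Visit 2 on | Due | Minimum taken | Share of due |
|---|---|---|---|
| Day 11 | 80 | 32 | 40.0% |
| Day 14 | 104 | 56 | 53.8% |
| Day 15 | 112 | 64 | 57.1% |
| Day 17 | 128 | 80 | 62.5% |

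Check for Day 14: 240 − 104 = 136 remain, and 56 + 136 = 192.

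Thus, unless dosing to date is below these shares, Visit 2 cannot establish that a subject will fail the 80% rule.

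**Cost of a removal to the planned analysis.** One subject is 1/25 = 4% of an arm. With equal standard deviations and k subjects lost from one arm, the standard error of the between-arm difference is multiplied by √[(1/(25 − k) + 1/25) / (2/25)]:

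- k = 1: 1.0104
- k = 2: 1.0215
- k = 3: 1.0335

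The protocol gives no removal rate, so 1 to 3 is an assumed range. The formula applies only to removed subjects who would have reached 80% and met the other conditions of Section 8.2. Those ending below 80% would have left the per-protocol set anyway.

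**The case against.** The strongest reply is that the protocol grants a permission and orders nothing. The sentence on non-compliance is a definition. Within its own paragraph, the wording on discontinuation attaches to subjects who entered in violation of the protocol. The link to removal comes from the lead-in above it. The planned response to poor dosing at Visit 2 is encouragement, no capsule count is made there, and returned capsules are first counted at the visit where the outcomes are taken. The harmful sequence therefore needs an investigator to act on self-report, against the purpose of the contact. The table's shares are also limits: they require every remaining capsule to be taken, so they show what is possible, not what is likely.

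Most of this stands, and it limits the point. A reader might infer that the protocol requires removal for missed doses, or that the removal criterion contradicts Section 8.2. The documents support neither, because removal is discretionary and the two rules can coexist. A reader might also infer bias between arms. Nothing in the protocol shows that removals would differ by arm, and the decision is made with pouches labelled only A or B.

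Nor is safety information wholly lost. Visit 2 reviews adverse events, events are followed up, and any post-randomization safety information qualifies a treated subject for the Safety Population. The protocol does not forbid an assessment at discontinuation, although it schedules none.

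The objection does not remove the central point. A definition of non-compliance placed under criteria for removal has no other evident function, and it carries no threshold.

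**Conclusion.** The point holds as a small, avoidable weakness. The protocol allows removal from the study for any imperfect dosing, before its own 80% count can be made, and schedules nothing afterwards.

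Its size depends on the subject:
- **Would have reached 80% and met the other per-protocol conditions:** the loss to the planned effectiveness analysis is about 1.0% in standard error for one such subject, and up to 3.4% for three in one arm.
- **Would have ended below 80%:** nothing is lost to the per-protocol analysis. What is lost is the Visit 3 safety and laboratory data, and JKOM and JOA for any supportive all-randomised analysis.

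This rests on reading the sentence as a removal ground because of where it stands, on no unscheduled assessment being made, and on equal standard deviations in the arms. How often it would happen is unknown. It is a cheap improvement worth considering and does not threaten the trial's validity. Missed visits and refused procedures, which the same sentence names, are outside this point.

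**What to change.** Amend Protocol violation to state that:

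1. Imperfect dosing alone is not a ground for removal from the study. The investigator may still stop the supplement for safety, including for excess intake.
2. Visit 3 JKOM, JOA, adverse-event and laboratory assessments are taken from every subject with imperfect dosing who still consents and has not been withdrawn under Clinical reasons.

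In Removal by Qualified Investigator, make the general discretion subject to item 1. Otherwise the same removal stays possible under the broader power. Clinical reasons stays as it is, including "All serious adverse events will result in withdrawal from the trial". Section 8.2 also needs no change: the 80% count at Visit 3 remains the only dosing criterion for per-protocol membership, alongside its other conditions.

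The cost is a short wording amendment and a few Visit 3 assessments that are already scheduled. Some will be in subjects who end outside the per-protocol set. Their JKOM and JOA have no stated effectiveness use at present, but their adverse-event and laboratory data would serve the Safety Population.

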# TEST SUPPLEMENT

## Manufacturing and Storage

The test supplement will be provided by the study sponsor Sunsho Pharmaceutical Co. Ltd. The test supplement will be carefully stored at Fukushima Orthopedic Clinic in a lockable, limited access area, accessible only to authorized study team personnel in compliance with pertinent regulations. The products will be stored at room temperature and will not be exposed to direct sunlight or heat.

All unused test supplement will be returned to the study sponsor at study closeout (within one month of last subject visit).

The test supplement is manufactured by Sunsho Pharmaceutical Co. Ltd.

